### Participant timeline

At each NICU, a research coordinator screens all infants for eligibility and maintains a log of all inclusions/exclusions. Parents are approached by a study investigator who is not the attending neonatologist of that baby, and informed parental consent is obtained prior to the first planned extubation. Participants have the cardiorespiratory signals recorded immediately prior to their first planned extubation and clinical information is prospectively collected at various time points from birth until death, discharge or transfer from the NICU, as presented on the SPIRIT participant timeline in Table 3.

**Table 3 Tab3:**
[figure not shown]
Participant timeline according to the SPIRIT guidelines

-t_1_ = birth to extubation

0 = immediate period prior to initiation of data acquisition

t_1_ = 60-min recording prior to extubation

t_2_ = 5-min recording prior to extubation

t_3_ = immediate period post-extubation

t_4_ = first 72 h period post-extubation

t_5_ = period between 72 h and 14 days post-extubation

t_6_ = discharge, death or transfer from the neonatal intensive care unit

### Sample size

The machine learning methods that will be used for this study have built-in mechanisms to guard against over-fitting the data (i.e., representing the training examples perfectly but having weak predictive power on new data). Consequently, traditional statistical approaches for determining sample size do not apply [65]. Therefore, sample size was estimated by applying a methodology proposed by Obuchowski and McClish and detailed by Zhou et al. [66, 67]. This method relies on estimating the prevalence of the disease of interest in the study population, estimating the variance of the receiver operating characteristics (ROC) curve based on a pilot study, and picking a required precision for the area under the curve (AUC). The prevalence of extubation failure was estimated conservatively to be 20%, based on both a review of the literature and the clinical collaborators’ experience. The variance in the AUC was then estimated by applying bootstrap methods to the data acquired in our pilot study. Using these values and an AUC precision of 0.1 led to an estimated sample size of 170 babies. This sample size would provide a minimum of 5 failure cases in each fold when performing 5-fold cross-validation, thereby ensuring a reliable measurement of generalization power [68]. Nevertheless, in the face of changing practice with the increasing use of HHHFNC post-extubation, and the uncertainty related to its impact on extubation failure rates in this population, the sample size was conservatively increased to 250 patients. As for the prospective validation of APEX, the sample size of 50 infants has been chosen large enough to demonstrate the anticipated benefits and feasibility of the predictor.

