## Background

### Scope of the problem

Approximately 15,000 infants are admitted to the neonatal intensive care unit (NICU) in Canada each year, of which 11% are extremely preterm (gestational age (GA) ≤ 28 weeks) [1]. Due to lung immaturity, weak respiratory drive and surfactant deficiency, the majority of these infants require endotracheal intubation and invasive mechanical ventilation (MV) during their first days after birth [2]. In a recent large epidemiological study, 85% of extremely preterm infants required MV at some point during hospitalization, most of whom were intubated in the delivery room [3]. Amongst infants with GA of 24 and 25 weeks, 99% and 95% required MV, respectively [3]. Therefore, MV remains an integral part of respiratory management of extremely preterm infants.

Although life-saving at first, prolonged MV has been linked to several adverse outcomes, including ventilator-associated pneumonia, airway trauma and bronchopulmonary dysplasia (BPD) [4]. BPD is the most serious pulmonary morbidity, having been associated with long-term respiratory and neurodevelopmental impairments [5], as well as important social and economic burdens [6]. The duration of MV is a strong predictor for developing BPD; each additional week increases the odds of BPD by a factor of 2.7 [7]. Consequently, clinicians make every attempt to limit its duration and advocate for extubation as early as possible [8]. However, premature extubation carries its own hazards, including lung derecruitment, compromised gas exchange, inspiratory muscle fatigue and ultimately the need for reintubation [9–11]. Indeed, rates of extubation failure in extremely preterm infants have been reported in the literature to be anywhere from 10% to 70%, depending on the population studied and the time frame or criteria used to define failure [12, 13].

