### Objectives

This project aims to develop an automated predictor to help physicians determine when extremely preterm infants are ready for extubation, using the combination of clinical tools along with novel and automated measures of cardiorespiratory variability. The research objectives will be accomplished in this following sequence:Generate a library of clinical data and cardiorespiratory signals in preterm infants prior to extubation;Develop a robust model for prediction of extubation readiness, i.e. referred to as APEX (Automated prediction of extubation readiness);Prospectively validate the clinical utility of this prediction model

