The development of APEX as described above will use a variety of specialized software tools. These provide the flexibility necessary for exploratory research but may not be suitable for clinical use. Therefore, we will develop an integrated software system that will perform all the data acquisition, signal analysis, and classification operations needed to predict extubation outcome with a user-friendly interface suitable for medical personnel in the NICU. Prototypes of the package will be developed and tested using MATLAB’s interactive environment, which supports all the needed algorithms and provides a complete set of tools for graphical interface development. Once a prototype is available, its clarity and usability will be assessed by recruiting clinicians from the NICUs (neonatologists, respiratory technicians) to test the package in a simulated setting and provide feedback. Once the package is finalized, the MATLAB compiler will be used to generate a stand-alone application that will be installed on the data acquisition machines.

The performance of APEX will then be validated in a prospective study of an additional 50 preterm infants. These will be used only to evaluate the performance of the predictor in the clinical setting. Moreover, the APEX classification algorithm and parameters will be pre-specified and used for all infants. Patient recruitment, acquisition, and follow-up will be the same as for the original study. However, immediately following completion of the cardiorespiratory recordings, APEX will carry out the signal analysis and classification computations to assign the infant to FAILURE, SUCCESS, or UNCERTAIN groups (see ‘Statistical methods’ below). This APEX classification will not be available to the attending staff and so will not influence clinical care.

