#### Prospective APEX validation

The predictive validity of APEX in the clinical context will be evaluated in two ways.

First, we will evaluate the accuracy with which infants are assigned to the high confidence SUCCESS and FAILURE groups by comparing the predicted and observed outcomes. We expect that infants will be assigned to these high-confidence groups with high accuracy. Second, the clinical utility of the approach will also depend on the benefits and costs associated with its potential impact on patient outcome. The **benefits** of using the method can be summarized in terms of the IR, the proportion of extubation failures that could potentially be prevented. The **costs** can be summarized in terms of the FDR, the proportional of infants incorrectly assigned to failure class. Our objectives are to obtain an IR of 0.8 and an FDR of less than 0.5. This would translate into reducing the extubation failure rate from an estimated 20% to less than 5%, at the cost of prolonging the ventilation of one infant for each extubation failure prevented.

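### Fifty validation infants can show feasibility and better-than-chance discrimination, but not the IR and FDR targets that the protocol says they will demonstrate

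*Protocol article*

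**What the plan says.** The third objective of the protocol article is to "Prospectively validate the clinical utility of this prediction model". Under Prospective validation of APEX, the plan states: "The performance of APEX will then be validated in a prospective study of an additional 50 preterm infants". These infants serve only for evaluation, with the algorithm and its parameters fixed beforehand. The Sample size section justifies the number in one sentence: "the sample size of 50 infants has been chosen large enough to demonstrate the anticipated benefits and feasibility of the predictor". No precision, power or comparator accompanies it. The only sizing calculation in that section (AUC precision 0.1, giving 170, later raised to 250) is for the development cohort.

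The statistical section on prospective validation says what the benefits are: they come from "using the method can be summarized in terms of the IR, the proportion of extubation failures that could potentially be prevented". The targets follow: "Our objectives are to obtain an IR of 0.8 and an FDR of less than 0.5". Their expected consequence is also given: "This would translate into reducing the extubation failure rate from an estimated 20% to less than 5" per cent. The planning failure rate appears under Sample size: "The prevalence of extubation failure was estimated conservatively to be 20" per cent.

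**The concern.** The adequacy of the 50 infants is asserted, not left open, and the plan supplies enough figures to test it. IR has the number of failures as its denominator, and FDR has the number of infants placed in the FAILURE class. Neither denominator is 50, and at the planning failure rate both are small.

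This cohort is the only independent test of the fixed algorithm. The clinical use foreseen in Statistical methods is to delay extubation in infants predicted to fail. If IR and FDR are read as point estimates against 0.8 and 0.5, a predictor that truly meets both targets could be reported as falling short. An observed IR of 0.8 could equally be reported as demonstrated when the data remain compatible with identifying fewer than half of the failures.

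**Working it through.** **Inputs from the protocol article.** Validation size 50 and failure rate 20% (Sample size); IR target 0.8 and FDR target below 0.5 (Prospective APEX validation). IR = failures assigned to FAILURE / all failures. FDR = successes assigned to FAILURE / all infants assigned to FAILURE (Statistical methods).

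**The plan's own figure.** Residual failure rate = 20% × (1 − IR) = 20% × (1 − 0.8) = 4%, which is below 5%. This reproduces. No calculation is given for the 50, so there is nothing to reproduce there.

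**Step 1: denominators.**
- Expected failures: 50 × 0.20 = 10. The 95% range of a Binomial(50, 0.2) count is 5 to 16.
- Failures flagged at IR 0.8: 0.8 × 10 = 8.
- Infants flagged at the FDR limit of 0.5: 8 / (1 − 0.5) = 16, of whom 8 are successes.

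**Step 2: exact (Clopper-Pearson) 95% intervals for an on-target result.**
- IR 8/10 = 0.80: 0.444 to 0.975, mean half-width (0.975 − 0.444)/2 ≈ 0.27.
- FDR 8/16 = 0.50: 0.247 to 0.753, mean half-width (0.753 − 0.247)/2 ≈ 0.25.

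**Step 3: what this means for the promised fall in failures.** Applying 20% × (1 − IR) to the ends of the IR interval gives 20% × (1 − 0.975) = 0.5% and 20% × (1 − 0.444) = 11.1%. A residual rate below 5% requires IR above 1 − 5/20 = 0.75, and the interval lies on both sides of 0.75.

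**Step 4: chance of observing IR ≥ 0.8 and FDR < 0.5 together in 50 infants.** The number of failures is Binomial(50, 0.2), flagged failures are Binomial(failures, IR), and flagged successes are Binomial(successes, 1 − specificity). Specificity here means the share of successes not placed in FAILURE, and it is an assumption in every row. True FDR = 0.8 × (1 − spec) / [0.8 × (1 − spec) + 0.2 × IR].

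| True IR | Specificity | True FDR | Chance of showing both targets |
|---|---|---|---|
| 0.8 | 0.9 | 0.08/(0.08 + 0.16) = 0.33 | 51% |
| 0.8 | 0.8 | 0.16/(0.16 + 0.16) = 0.50 | 30% |
| 0.7 | 0.85 | 0.12/(0.12 + 0.14) = 0.46 | 20% |
| 0.9 | 0.9 | 0.08/(0.08 + 0.18) = 0.31 | about 79% |
| 0.5 | 0.9 | 0.08/(0.08 + 0.10) = 0.44 | 3% |
| 0.5 | 0.7 | 0.24/(0.24 + 0.10) = 0.71 | 0.3% |

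The first row is the relevant one: a predictor with IR at its target and FDR well inside its limit shows both targets about half the time. The second row sits on the FDR boundary, so strictly it does not meet the objective.

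**Step 5: what the sample can show.** In the on-target table, 8 of 10 failures and 8 of 40 successes are flagged; Fisher's exact p = 0.0007. Flagging 16 of 50 infants at random would give IR 16/50 = 0.32 and FDR 0.80, and both lie outside the intervals in step 2.

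**Step 6: comparison with the development cohort.** 250 × 0.20 = 50 failures. An IR of 40/50 has an exact 95% interval of 0.66 to 0.90. Treating cross-validated predictions as independent makes this approximate.

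**The case against.** The plan sets no null value, error rate or required precision for the 50 infants, and it phrases 0.8 and 0.5 as aims, without a pass/fail rule. Against a predictor of no value, 50 infants are enough: step 5 shows a clear separation, and power against no association, averaged over the random counts, is about 93%. The feasibility half of the sentence is not in dispute. Staff do not see the classification, the Discussion limits the tool's validity until further validation, and cross-validation in 250 infants already provides a more precise estimate. The plan also lists a separate evaluation, the accuracy within the high-confidence groups. The failure rate could also be higher: "rates of extubation failure in extremely preterm infants have been reported in the literature to be anywhere from 10% to 70" per cent. At 30% there would be 15 failures, and 12/15 has an interval of 0.52 to 0.96.

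Most of this stands, and it limits the point. It does not support the sentence in the Sample size section, because the benefits named there are defined by the IR target and the fall in failures, not by discrimination better than chance. The planning rate is 20%, and even 12/15 leaves IR values well below 0.75 inside its interval.

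A reader might infer more than the documents support:
- **That no calculation could justify 50 infants, or that the results would be mostly noise.** Step 5 contradicts both.
- **That a poor predictor would often appear to succeed.** With a true IR of 0.5 and specificity of 0.7 to 0.9, it shows both targets only 0.3% to 3% of the time. The 20% row is a predictor that meets the FDR limit and narrowly misses on IR.
- **That choosing the threshold for the largest IR forces the true FDR close to 0.5.** The plan speaks of an acceptable FDR without giving its value.

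**Conclusion.** The point holds, at moderate severity. The statement that 50 infants can demonstrate the anticipated benefits is unsupported and conflicts with the plan's own 20% failure rate. About 10 failures give an on-target IR an interval of 0.44 to 0.97 and an on-target FDR an interval of 0.25 to 0.75. The data could not confirm a fall in failures to below 5%, and a predictor with true IR 0.8 and FDR 0.33 would miss at least one target about half the time. The main weakness is therefore failing to confirm a good predictor and estimating its performance imprecisely; endorsing a bad one is much less likely.

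This rests on the 20% failure rate, on exact two-sided 95% intervals, and on the assumed specificities in step 4. It is a flaw in a stated claim and is not a detail that an analysis plan could supply, since no analysis makes about 10 failures precise.

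**What to change.** In the Sample size section, replace the claim about demonstrating benefits with a description of the 50 infants as a feasibility study and preliminary evaluation of the fixed algorithm. State the expected number of failures (about 10, range 5 to 16) and the expected 95% interval widths (about ±0.25 for each of IR and FDR).

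In the section on prospective validation, keep 0.8 and 0.5 as aims, report IR and FDR with exact 95% intervals, and make no claim from point estimates alone that either was met or missed. Present the cross-validated estimates from the 250 infants, with intervals, alongside.

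The cost is a weaker stated claim; no patients are added.

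If the sponsor prefers to keep the claim, the cohort has to be sized to a stated precision. For an assumed half-width of 0.15, IR needs 1.96² × 0.8 × 0.2 / 0.15² ≈ 28 failures, or 28/0.20 = 140 infants. FDR needs 1.96² × 0.25 / 0.15² ≈ 43 flagged infants, or 43/0.32 ≈ 135 infants, where 0.32 = 16/50.

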### Recruitment

Several strategies have been put in place to ensure steady patient recruitment at each participating site. First, the research coordinators promptly identify eligible patients and approach the parents for consent well before extubation. The coordinators follow the infant’s daily status and proactively organize with the attending physician for the cardiorespiratory recordings to be made prior to extubation. In addition, in order to raise awareness of all NICU personnel (i.e. neonatologists, nurses, respiratory therapists, neonatal nurse practitioners and trainees) about the study, routine activities have been instituted at each unit, in the form of information sessions, in-service training and presentations.

### Data collection methods and data management

In order to harmonize the process of cardiorespiratory acquisition and clinical data collection, assessors from all recruiting sites will get formal training by the same research investigator. Assessors will also receive standardized instructions describing all procedures step-by-step, tips for troubleshooting signal acquisition and definitions of clinical data items. All cardiorespiratory signals will be recorded using a pre-set template from PowerLab’s data acquisition system, thereby ensuring homogeneous sampling methods and a controlled vocabulary of comments added by the investigators during the recording. As for clinical data, it will be entered manually then transcribed into a standardized Microsoft Excel TM (Microsoft Corporation) template that uses multiple layers of quality control to minimize data transcription errors and regulate the type of information entered. Both cardiorespiratory signals and clinical data files will be copied to an encrypted USB key and stored in a locked cabinet that is only accessible to the research investigators. This data will be kept for a period of 7 years after the end of the study, in accordance with the Research Ethics Board guidelines.

Results from the first objective will yield a large, complex dataset that needs to be properly organized, cataloged and readily accessible to investigators from multiple disciplines and geographically-distinct institutions. To facilitate this collaboration, the cloud-based storage and sharing platform Dropbox for Business™ (Dropbox, Inc.) will be used. At the same time, it is important to ensure that the cloud-based file-sharing environment is secure and free of patient identifiers. Thus, our group has developed and implemented an automated anonymization protocol for that purpose, as described in detail elsewhere [69]. In a nutshell, the original cardiorespiratory signals and clinical data are first transferred to a secure repository only accessible to a single administrator responsible for implementing the protocol. The files are then systematically de-identified and automatically transferred to the collaborative repository, where all team members can view the anonymized data in real time [69].

Despite the aforementioned safeguards during the data acquisition process, issues may still arise in the quality of clinical files (e.g. transcription errors, missing data or outlier values) and cardiorespiratory signals (missing or disconnected signals, inadequate recording durations). For those reasons, our group has additionally put in place an algorithm for automated validation and quality control of all files, as described in detail elsewhere [70]. Through automatically-generated summary reports, the completion status of all files is shown and problems are flagged. Moreover, the behavior of various signal properties and clinical variables are described within each site and compared between sites. As a whole, this ensures that all issues are identified and addressed in a timely fashion, that the data quality is uniform across sites and that all included files are validated prior to analysis.

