**Fig. 2 Fig2:**
[figure not shown]
Representative example of a cardiorespiratory recording from a preterm infant. The signals displayed, from top to bottom, are: electrocardiogram, rib cage movements, abdominal movements, sum of rib cage and abdominal movements, oxygen saturation and photoplethysmography

Data is acquired from each infant while quiet, stable and in supine position, during 2 continuous recording periods immediately preceding extubation:A 60-min period while the infant receives any mode of conventional MV. These data will be used to characterize the HRV properties of the infant prior to extubation. However, this data may not be suitable for characterizing RV, since the respiratory pattern is still influenced by the ventilator.A 5-min period will be used to record the respiratory parameters. During this time, the ventilation will be switched to endotracheal CPAP at the same positive end-expiratory pressure level used during the first recording period, so that the cardiorespiratory patterns are controlled by the infant.

II. *Acquisition of clinical data.*

The key clinical variables recorded for each infant are summarized in Table 2, and the following respiratory outcomes are recorded while the infant is hospitalized in the NICU:

**Table 2 Tab2:** Clinical variables to be collected for infants enrolled in the study

Antenatal and maternal variables	Mother age, parity, complications during pregnancy, maternal medications, intra-uterine growth restriction, mode of delivery, multiple birth, use of antenatal steroids, rupture of membranes, use of antibiotics during labor, histological chorioamnionitis.
Infant characteristics pre-extubation	Gender, birth weight, gestational age, Apgar scores (1, 5 and 10 min), cord blood gases, use of surfactant (age, dose), use of antibiotics and caffeine administration prior to extubation (age and dose).
Infant characteristics at time of extubation	Weight at extubation, age and post-conceptional age at extubation, ventilator mode, peak inflation pressure, positive end-expiratory pressure, mean airway pressure, tidal volume, set inspiratory time, ventilator rate, fraction of inspired oxygen (FiO_2_), oxygen saturation and blood gas
Infant characteristics post-extubation	Type of non-invasive respiratory support, interface used, settings, FiO_2_ and blood gas
Primary extubation outcome	Fulfilling extubation failure criteria within 72 h from extubation

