**Fig. 3 Fig3:**
[figure not shown]
Sample epochs of respiratory data from a preterm infant displaying the respiratory patterns detected automatically by AUREA. AUREA - Automated Unsupervised Respiratory Event Analysis system **a** Pause (PAU), **b** Movement artifact (MVT), **c** Asynchronous breathing (ASB) and **d** Synchronous breathing. Horizontal *dotted* lines indicate the center of each segment

The performance of AUREA’s assignment of respiratory patterns will be compared with results of an experienced manual scorer, and fine-tuned accordingly.

*B)*
*Heart Rate Analysis.* ECG signals acquired during the recording periods will be analyzed by first converting the ECG signal into a point process by identifying the maxima of the R wave. The resulting signal will then be low-pass filtered using the French-Holden algorithm [59] to generate a continuous HR signal. Instantaneous estimates of power in the: i) Very Low Frequency (VLF) = 0.01–0.04 Hz; (ii) Low Frequency (LF) = 0.04–0.2 Hz, and (iii) High Frequency (HF) = > 0.2 Hz bands will be determined by passing the continuous HR signal through a bank of band-pass filters with appropriate cut-offs. These filters will be implemented in the time domain as symmetric, two-sided finite impulse response filters, making it possible to track changes in HRV as a function of time with no delay.

*C)*
*Pulse Oximeter Analysis.* The PPG signal will be analyzed to detect movement artifacts using an algorithm that computes and removes a moving average of the larger quasi-periodic pulse components. The RMS of the residual will be close to zero for clean signals and higher during movement artifacts. This metric is faster and performs better than other methods that use higher order statistics [60, 61]. Oxygen saturation and Pulse Transit Time (PTT) will be computed for artifact-free segments. The PTT estimates the time elapsed between the R-wave of the ECG and the peripheral PPG pulse [62], and has been shown to be useful in the diagnosis of Obstructive Sleep Apnea Syndrome [63].

*D)*

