*Stationarity.* Each metric is computed for each sample. The behavior of any given sample may vary randomly and/or as a function of time. This will likely occur during the 5-min period on endotracheal CPAP as the infant adapts to a sudden change on respiratory load. Consequently, the time course of each metric will be inspected to ensure that it is stationary. If not, we will first try to break the data set into shorter, quasi-stationary segments. Should this fail, the metric’s time-varying behavior will be described using time series analysis methods.

*E)*
*Feature Detection.* We will determine which statistical properties of these metrics describing cardiorespiratory activity are likely to be useful for predicting extubation readiness. To do so, subjects will be separated into two groups, defined by extubation failure or success, and the probability density (PDF) of each metric will be computed and compared. Differences in the variability of a metric will be revealed by changes in the shape of the PDFs; increased variability should result in a broader PDF while a decrease will result in a narrower PDF. In pilot studies, we found that the interquartile range was a useful feature to quantify variability. However, the shapes of the PDFs may suggest other statistics to use as features. The respiratory patterns generated by AUREA, along with the clinical variables collected, will be subjected to a similar analysis. The set of cardiorespiratory and clinical features with discriminative ability will be selected for use with machine learning methods to build the final predictor.

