### Statistical methods

#### Machine learning algorithms

The performance of the entire machine learning algorithm (described in ‘data analysis’ above) will be assessed using cross-validation, a standard approach that consists of splitting the data into several sub-sets (‘folds’) while ensuring that the distribution of the data in each subset is similar. Some subsets are used for feature selection and classifier training, while others are used for computing an unbiased estimate of the specificity and sensitivity of the classifiers. Each infant will be assigned to one subset of the data, such that data from the same infant will not be used both for training and testing. We will use stratified 5-fold cross-validation, which ensures that reliable estimates of the sensitivity, specificity, and variance of the predictors can be obtained. ROC curves reflecting the sensitivity and specificity trade-off will be produced and used to analytically determine the best trade-off from the point of view of clinical practice [57].

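### The whole team can see outcomes beside the signals, and no masking is stated for those who segment, score or clear recordings, so cross-validated performance may be optimistic

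*Protocol article*

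**What the plan says.** **Access.** Under Data collection methods and data management, "the original cardiorespiratory signals and clinical data are first transferred to a secure repository" run by a single administrator. De-identified copies then pass to the collaborative repository, "where all team members can view the anonymized data in real time". Table 2 lists the primary outcome, "Fulfilling extubation failure criteria within 72 h from extubation", among the clinical variables, together with failure up to 14 days and reintubation. De-identification removes identity, not outcome.

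**Steps that involve judgement.**
- Phase I, part D (Stationarity): "the time course of each metric will be inspected to ensure that it is stationary". If it is not, "we will first try to break the data set into shorter, quasi-stationary segments"; if that fails, a time-series description is used. No criterion is given, and the article expects non-stationarity to be likely in the 5-min CPAP recording.
- Phase I, part A: AUREA's pattern assignment "will be compared with results of an experienced manual scorer, and fine-tuned accordingly".
- Data management: an automated algorithm checks files and flags problems. Flagged issues are then dealt with, so that "all included files are validated prior to analysis". Who resolves them, and by what rule, is not stated.

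**Claim for the estimates.** Under Machine learning algorithms, some folds serve feature selection and training, while "others are used for computing an unbiased estimate of the specificity and sensitivity of the classifiers".

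**Masking.** The only masking stated is in the prospective validation, where the APEX class is kept from attending staff.

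**The concern.** Five-fold cross-validation protects against a classifier being tested on infants it was trained on. It does not protect against a feature value that already carries the outcome before the folds are formed. If an analyst who can see that an infant failed decides where to cut that infant's recording, the choice can drift towards the expected pattern, for example lower variability in failures. The drift is present in test folds as well as training folds, so the held-out infants appear to confirm it.

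At stake are the development estimates: sensitivity, specificity, the ROC trade-off, and the bootstrap threshold that is to give the largest IR at an acceptable FDR. A classifier tuned on such differences would meet data without them once an automated bedside package does the processing.

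**Working it through.** No figure in the article is contradicted, so the check has three parts: the path from access to bias, its possible size under assumed settings, and the validation cohort.

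**1. Path.**
- Outcomes and signals sit in one place open to the team (Data management; Table 2).
- Segmentation acts on the data from which features are computed, by inspection and without a stated rule (Phase I, part D).
- The cross-validation text covers feature selection and training. It does not name inspection or segmentation as done within folds.
- So if segmentation is outcome-aware, test-fold features are affected and the unbiasedness claim does not hold.

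**2. Yardstick.** The Sample size section uses an AUC precision of 0.1 and 20% failures to reach 170. Its AUC variance is not given. With the binormal formula, V = 0.0099·exp(−A²/2)·[5A² + 8 + (A² + 8)/R], where A = √2·z(AUC) and R = 0.8/0.2 = 4. At an assumed AUC of 0.79, V = 0.0869. Failures needed are 1.96² × 0.0869/0.1² = 33.4, rounded up to 34, and 34/0.2 = 170. Assumed AUCs of 0.77 to 0.80 give 175 to 165. So 0.1 reads naturally as a 95% half-width.

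**3. Size in development (all settings assumed).** There are 250 infants, 250 × 0.20 = 50 failures, five features, a linear discriminant and stratified 5-fold cross-validation. In a share of infants the most hypothesis-consistent of three candidate segments is always taken. New infants are processed without knowledge of outcome.

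| Features | Share | CV AUC | New-infant AUC | Excess |
|---|---|---|---|---|
| No information | 0 | 0.500 | 0.501 | 0.00 |
| No information | 25% | 0.545 | 0.499 | 0.05 |
| No information | 50% | 0.641 | 0.500 | 0.14 |
| Informative | 0 | 0.746 | 0.750 | 0.00 |
| Informative | 25% | 0.811 | 0.752 | 0.06 |
| Informative | 50% | 0.866 | 0.756 | 0.11 |

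Milder settings give less:
- *Two candidate segments, no information, segment correlation 0.5 or 0.8.* CV AUC is 0.501 or 0.505 at a 10% share, 0.526 or 0.510 at 25%, and 0.584 or 0.536 at 50%. Runs without outcome-aware choice lay between 0.487 and 0.504, so the 10% result cannot be told from none.
- *Two versions correlated 0.6, discretion in 20 to 40% of records, favoured version taken 60 to 75% of the time.* AUC rises from 0.50 to 0.51–0.54 for one feature and to 0.52–0.60 for a sum of six.

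**4. Validation cohort.** The algorithm and its parameters are fixed in advance and run straight after the recording, before a 72-h outcome exists. The class therefore cannot be shaped by the outcome. What is not fixed in the text is when a validation file would be ruled unusable. At 20%, 50 infants give 10 failures. As an invented example, 7 of 10 identified is an IR of 0.70; if two missed failures were excluded it becomes 7/8 = 0.88, past the 0.8 target. Likewise an FDR of 9/16 = 0.56 becomes 6/13 = 0.46 if three false alarms were excluded, below the 0.5 limit.

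**The case against.** The strongest reply is that access is not use. A reader might infer that segmentation and scoring are in fact done with the outcome in view. The article says only that members are able to view the data, and it refers its sharing and quality-control workflows to other publications. That stands, so the point must be conditional. It does not dispose of it, because the all-member, real-time access is a stated arrangement that a masking rule elsewhere would have to qualify.

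Other stronger readings are also unsupported:
- *That people rule files valid by hand.* The article describes an automated algorithm; only the resolution of flags is open.
- *That AUREA is tuned to extubation outcome.* It is tuned to scored breathing patterns, once for the algorithm, and its metrics are automated. This limb is weak.
- *That the validation result is compromised.* The locked, immediate classification prevents that, and the article describes no late exclusion of validation files. The ratios in part 4 show only how sensitive a sample of 10 failures is.

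The stationarity text can also be read as one decision for a whole metric rather than a choice per infant. If a single rule were applied alike to all records, the mechanism would largely vanish. But no such rule is stated.

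Finally, testing the automated package in 50 new infants could expose inflated development figures. With 10 failures, however, an IR of 0.8 has a standard error of √(0.8 × 0.2/10) = 0.13, so only gross inflation would show.

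**Conclusion.** The point holds in conditional form. The article opens outcomes to everyone who may handle the signals and states no mask for re-segmentation, manual scoring or the resolution of flags. Segmentation is the limb that matters most. If it is done per record with the outcome visible, the cross-validated sensitivity and specificity, and the threshold built on them, may be optimistic, and cross-validation cannot correct this.

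The size cannot be derived from the article. The simulated excess spans essentially nothing to about 0.14 in AUC. It depends wholly on the assumed share of discretionary records, the number of candidate segments and how consistently the favourable one is taken. Only the most adverse settings reach or exceed the plan's AUC precision of 0.1. In the validation cohort the APEX class is sound; the residual risk is confined to a file exclusion decided after class and outcome are known.

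**What to change.** **Development.** Choose one of two routes:
1. The administrator who already runs the de-identification withholds the outcome fields from those who resolve signal flags, segment recordings and score patterns by hand, until those steps are frozen and dated for each record.
2. A fixed, automated stationarity and segmentation rule is written down and applied to all records.

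Outcomes are then released for the Phase I group comparison, feature choice and classifier training, with feature selection kept inside the folds. The freeze should cover the signal steps, not the list of features, because Phase I, part E, deliberately lets the outcome-group distributions suggest features.

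Enrolment has run since September 2013, and outcomes already shared cannot be hidden again. For those infants the masked route needs staff who have not seen the outcomes; the automated rule is the alternative.

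**Validation.** Settle the usability of each signal file from the signal alone, and record it before the APEX class and the 72-h outcome reach whoever decides.

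**Cost.** The administrator and the two-stage repository exist, so the main change is to permissions plus a dated freeze. Analysts receive outcomes later, and data checkers who need outcome fields for quality control must be kept separate from signal decisions.
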